### Sham-acupuncture group

Patients in the sham-acupuncture group will receive the same sessions of treatment using Streitberger needles at the same acupoints. Streitberger needles have the appearance of the real needles, however, they will not penetrate the skin. They can be placed at the same acupoints as the real acupuncture group, and held in position by adhesive plaster with a plastic ring, which is conducive to the blinding purpose [38]. When the needle is pushed against the skin, a pricking sensation just like the real insertion will be generated. However, as the pressure increases, the needle shaft will bounce back into the handle, which guarantees the skin unbroken and makes an artificial impression of needle insertion (Fig. 2). Other procedures will be the same with the real acupuncture group, including the application of adhesive plaster and plastic rings.

**Fig. 2 Fig2:**
[figure not shown]
Structure of Streitberger needle. (1) Needle handle (2) Needle rod (3) Blunt tip of the placebo needle (4) Plastic ring (5) Plastic cover (6) Sharp tip of the real needle

### Decongestive therapy

For ethical considerations (the interest of participants in sham-group), every participant in both groups will receive the same usual care of decongestive therapy after treatment, which includes a daily manual lymph drainage, gentle exercise, applying moisturizer, and wearing elastic compression garments. Table 2 details the duration, frequency, executor, and location of each step. For participants who take other practice, detailed reports will be required.

**Table 2 Tab2:** Overview of standard decongestive therapy contents

Standard decongestive therapy	Duration	Frequency	Location	Record	Note
Manual Lymph Drainage	30 min	Daily	Hospital	Massage Therapist	Meticulous records are needed otherwise.
Applying Moisturizer	3 times	Daily	Home	Participant	
Gentle Exercise	2 h	Daily	Home	Participant	
Wearing Compression Garment	3 h	Daily	Home	Participant	

### Patient health monitoring

For each participant in both groups, blood pressure and pulse rate will be monitored following every treatment session, whereas routine blood test, ECG test, renal function test and liver function test will be conducted every 2 weeks (Table 1). These data will be monitored closely by DSMB during the trial.

Moreover, as cuts and other breakage of the skin would incur infection and the deterioration of lymphedema, all participants will be warned. For those developing sudden onset of infection, the treatment should be discontinued till the patients have fully recovered and the coordinator in charge should be contacted as soon as possible. In other cases like serious complications and occurrence of other emergencies, where patients are unfit for further therapies, they will be persuaded to quit.

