**Methods/Design:**

Women who are clinically diagnosed as unilateral BCRL, with a 10% to 40% increase in volume compared to the unaffected arm, will be recruited. Following baseline assessment, participants will be randomized to either the real acupuncture group or sham-acupuncture group at a ratio of 1:1, and given a standard real acupuncture or sham-acupuncture treatment accordingly on both arms followed by the same usual care of decongestive therapy. Volume measurements of both arms will be performed for every participant after each treatment. Data collected at baseline and the last session will be used to calculate the primary outcome and secondary outcomes. Other data will be exploited for interim analyses and trial monitoring. The primary outcome is the absolute reduced limb volume ratio. Secondary outcomes are incidence of adverse events and change in quality of life. A t test or non-parameter test will be used to compare the difference between two groups, and assess the overall effectiveness of acupuncture using the SPSS software (version 12).

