### Real acupuncture group

Patients in the real acupuncture group will receive true acupuncture 3 times a week for 4 weeks (12 sessions) at 6 acupoints in each arm: Jianyu (LI 15), Jianliao (SJ 14), Binao (LI 14), Quchi (LI 11), Shousanli (LI 10), and Waiguan (SJ 5). These acupuncture points were selected on the basis of classic TCM record, the published literature [30–35], and the consensus between our experienced acupuncturists. Acupoints are detailed in Fig. 1. After the application of alcohol swabs, these acupoints will be covered by adhesive plaster with plastic rings, and stimulated by manual rotation of the needles accompanied by lifting and thrusting gently to make patients get de qi, which is a sensation of aching or distension or numbness elicited by acupoint stimulation [36, 37]. Then needles will stay put for 30 min.

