### Data collection

Before the first treatment session, every participant will get an assessment of both limbs by perometer, which is an automated infrared light digital scanner equipped with a microcomputer. When the limb is placed inside, the infrared light transmitters located on two sides of the perometer will be activated, and the blockage of the transmission of infrared light from both sides caused by the limb will be recorded and calculated. As the transmitters move along the limb, a series of images will be recorded. Hence a highly accurate measurement of the limb size and volume will be created. And these results will serve as the baseline data. Following the treatment of each session, participants in both groups will be asked to take assessments to get the interim data. Upon the last session, the assessments of both limbs will be adopted as the end-point data. For each arm, the measurement will repeat 3 times to ensure the reliability. Table 1 illustrates all the time points when measurements are taken during the whole procedure.

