### Primary outcome

#### Absolute reduced limb volume ratio (ARLVR)

The ARLVR is the proportion of absolute reduced limb volume in the affected arm after the therapy, compared with the absolute excess volume in the affected arm before the therapy. This index is inspired by the methods established by Anderson et al. [39] With all data collected at the end of the trial, the ARLVR will be calculated using the following formula:

$$ \mathrm{ARLVR}\ \left(\%\right)=\frac{\left({\mathrm{V}}_{\mathrm{AB}}\hbox{-} {\mathrm{V}}_{\mathrm{AL}}\right)\hbox{-} \left({\mathrm{V}}_{\mathrm{UB}}\hbox{-} {\mathrm{V}}_{\mathrm{UL}}\right)}{\left({\mathrm{V}}_{\mathrm{AB}}\hbox{-} {\mathrm{V}}_{\mathrm{AL}}\right)}\times 100\% $$

In particular, V_AB_ represents the volume of affected arm with lymphedema at baseline; V_AL_ represents the volume of affected arm with lymphedema at the last session; V_UB_ represents the volume of unaffected arm at baseline; V_UL_ represents the volume of unaffected arm at the last session.

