### Loss to follow-up and data management

In practice, however, participants might withdraw from the treatment program at any time. In that case, a call from the acupuncturist in charge will be given to the participant, and appropriate advice and assistance will be provided. If a participant insists on withdrawing from this trial, an instant evaluation of lymphedema status will be made, if it is possible. Complete case reports and case reports on loss-to-follow-up of the participants will be reported to the coordinators in charge every month. First-hand data will be recorded by the nurse and the acupuncturist. The coordinator in each center will collect and preserve the data every two weeks. When the trial is done, the aggregated data will be extracted by two independent researchers to guarantee the accuracy, and finally submitted to the principal investigator for analysis. During the whole process, the privacy of research participants will be fully protected.

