### Statistical and data analysis

Upon the receipt of the final data, the Kolmogorov-Smirnov test (K-S test) will be performed, followed by a test for homogeneity of variance to see whether the variances are equal between groups. If the data distribution fits a normal distribution with equal variance, the independent t test will be employed; otherwise, nonparametric test will be chosen to determine whether there is significant difference between the real acupuncture group and the sham acupuncture group. Moreover, one-way ANOVA will be performed to see whether there is significant difference between three centers. Analysis of covariance adjusted for clinical center and baseline will be applied on the condition that significant difference exists between three centers. In addition, regression analysis will be performed to analyze the effects of co-variances (risk factors) such as BMI, axillary lymph node dissection, postoperative radiotherapy, infection, and history of lymphangitis on the overall outcome of this treatment. A type I level error < 0.05 will be interpreted as statistically significant and 95% CI, mean, and SD will be calculated. Data analysis in this trial will consist of an intent-to-treat (ITT) analysis, a per-protocol (PP) analysis and an interim analysis. The ITT analysis will collect data from all the participants in this trial, and for those loss to follow-up, the last observation carried forward method will be implemented. As for the PP analysis, data collection will be rigorous, and only those participants who strictly comply with the protocol are eligible. The interim analysis in this trial performed by DSMB, will use the interim data collected during the trial to actively monitor the operating status of the trial and help find problems timely. All statistical analyses will be conducted using the SPSS software (version 12).

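### Stopping acupuncture is not separated from leaving the trial, so the week-4 outcome of patients who stop for complications is unobserved and an earlier value replaces it

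*Protocol article*

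**What the plan says.** All references are to the protocol article.

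- **Schedule.** The section on the real acupuncture group plans "true acupuncture 3 times a week for 4 weeks (12 sessions"); the sham group has the same schedule.
- **Unfit patients.** Under Patient health monitoring, for serious complications and other emergencies, "where patients are unfit for further therapies, they will be persuaded to quit". Infection is handled differently: "the treatment should be discontinued till the patients have fully recovered".
- **Endpoint.** Under Data collection, "Upon the last session, the assessments of both limbs will be adopted as the end-point data". The abstract agrees: "Data collected at baseline and the last session will be used to calculate the primary outcome and secondary outcomes". In the primary outcome formula, the follow-up term for the affected arm "represents the volume of affected arm with lymphedema at the last session". Volumes are also taken after every session, as interim data.
- **Withdrawal.** Under Loss to follow-up and data management, if a participant insists on leaving, "an instant evaluation of lymphedema status will be made, if it is possible". The same paragraph moves from leaving the treatment programme to leaving the trial without distinguishing the two.
- **Analysis.** Under Statistical and data analysis, "The ITT analysis will collect data from all the participants in this trial", and LOCF is used for those lost to follow-up.

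**The concern.** An ITT comparison at the end of a 4-week course needs the week-4 outcome of everyone randomised, including those who stopped treatment. Here the outcome measurement depends on attending a treatment session, so a patient who stops has no further measurement due.

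The patients affected are not a random subset. They stop because something went wrong, and the section on adverse events names worsening of the lymphedema as one possible event. That is the primary outcome moving the wrong way, so whether the week-4 value is missing can depend on what it would have been. LOCF then supplies a value from a different time and, possibly, a different clinical state.

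A second consequence concerns timing. A session-based endpoint is not a fixed date. A patient who pauses for infection and later completes the course is measured later than the others, after a longer stretch of the daily decongestive therapy given to both groups.

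**Working it through.** **1. What value enters the ITT analysis for a patient who stops early?** The text allows two readings of the last session.

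- If it means session 12, the patient has no endpoint and LOCF fills it.
- If it means the last session the patient came to, that session's volume is the endpoint.

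Under either reading the value is the last post-session volume or, where it was done, the exit evaluation. The week-4 volume is observed under neither.

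**2. The plan's own figures.** The sample size section assumes mean ARLVR (the primary outcome ratio) of 0.32 (SD 0.25) with real and 0.22 (SD 0.20) with sham acupuncture.

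- Planned difference: 0.32 − 0.22 = 0.10.
- Pooled SD: √((0.25² + 0.20²)/2) = 0.2264.
- Effect size: 0.10/0.2264 = 0.4417, as stated.
- Two-sided t test, α = 0.05, power 80%: 82 per arm, 164 in total (power 0.803), as stated.

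This point does not challenge the 164. The 0.10 serves below as the yardstick.

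**3. Effect of the substitution.** Let q be the share of an arm that stops early and b the mean gap in that arm (carried value minus true week-4 value). The shift in the estimated difference is

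shift = q_real × b_real − q_sham × b_sham.

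The document gives neither q nor b. Its only related figure is the planning allowance of 20% total loss to follow-up, or 0.20 × 200 = 40 patients, not split by reason or arm. The values below are assumptions, with stopping in one arm only:

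| Share stopping, q | b = 0.10 | b = 0.20 | b = 0.32 |
|---|---|---|---|
| 2% | 0.002 (2%) | 0.004 (4%) | 0.0064 (6.4%) |
| 5% | 0.005 (5%) | 0.010 (10%) | 0.016 (16%) |
| 10% | 0.010 (10%) | 0.020 (20%) | 0.032 (32%) |
| 20% | 0.020 (20%) | 0.040 (40%) | 0.064 (64%) |

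Percentages are of the planned 0.10. The 20% row assigns the whole loss allowance of one arm to such stops, so it is an outer bound rather than an expectation.

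**4. When the shift shrinks, vanishes or reverses.**

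- With the same gap in both arms and half the stopping share in the other arm, each entry halves: at 5% against 2.5% and b = 0.20, (0.05 − 0.025) × 0.20 = 0.005.
- With equal q and equal b in both arms, the shift is 0.
- If the exit evaluation catches a flare that would have settled by week 4, b is negative and the sign reverses: 0.05 × (−0.20) = −0.010 for stops in the real arm.
- If carried values show no treatment difference, the expected difference shrinks towards zero: 0.10 × (1 − 0.10) = 0.090 at 10% stopping in each arm, and 0.080 at 20%. With 100 per arm and unchanged SD, power is then about 0.80 and 0.70, against 0.875 with no such loss.

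**5. Timing after a pause.** If a patient pauses for k weeks and the missed sessions are made up, the last session falls at about week 4 + k; an assumed two-week pause gives week 6. The text does not say whether missed sessions are made up.

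**The case against.** The strongest case on the other side has five parts.

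- **Skin breakage and infection.** A reader might infer that the bias favours acupuncture, because only the real needle breaks the skin and infection is a named possible event. The document does not support this step. Infection leads to a pause until recovery, and the instruction to quit covers other cases, so the skin-breakage route runs mainly to patients who stay in. This objection stands.
- **The carried value may not predate the complication.** Volumes are taken after each session and an exit evaluation is foreseen, so worsening may already be in the carried value. This stands as a limit on size and direction. However, the evaluation is conditional on feasibility, is written for a participant who insists on leaving rather than for one persuaded to, and is made at exit, not at week 4.
- **The wording is ambiguous.** Quitting may mean quitting therapy only, and adverse events are to be followed until they settle, so contact after stopping is planned. True, but following an adverse event is not a scheduled volume measurement, and the ambiguity itself needs resolving.
- **The schedule may be elsewhere.** Table 1 is said to show all measurement times, and its content is not in the text at hand. It might add a visit. Even so, the withdrawal and analysis sections expressly put an earlier value in place of the endpoint.
- **ITT membership.** A reader might infer that these patients drop out of the ITT set. They do not; they remain in it with a carried-forward value. What is lost is their week-4 outcome.

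**Conclusion.** The point holds in a limited form. Followed as written, the rules leave the week-4 outcome of patients who stop for complications unobserved and replace it with an earlier value. This is outcome-related missing data built into the plan, and it could largely be avoided in a trial lasting only four weeks.

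Direction and size cannot be derived from the document. The example of 0.010, or 10% of the planned difference, rests on two assumptions (5% stopping in one arm only, and a gap of 0.20). It is zero if stopping and gap are equal across arms, and its sign can reverse. A claim that the plan favours acupuncture, or a fixed percentage of bias, would go beyond the text.

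The timing point is also conditional: the endpoint falls after week 4 for paused patients only if their missed sessions are made up. The plan should be changed, but the point does not invalidate the trial.

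**What to change.** Leave the clinical reasons for pausing or stopping treatment as they are, and amend the measurement and analysis rules:

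1. State that stopping acupuncture is not withdrawal from the trial, and define withdrawal as withdrawal of consent to further measurement. Align the sections on patient health monitoring and loss to follow-up with this.
2. Set the primary endpoint at 4 weeks after the first session, with a stated window, in place of the last session. Align the abstract, Data collection, the outcome definition and Table 1.
3. At that date, take perometer volumes of both arms and the PROMIS questionnaire for every randomised patient who has not withdrawn consent, however many sessions were received.
4. Use these values in the ITT analysis, and keep LOCF only for patients who are truly unobserved at that date.

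**Cost.** A short amendment and the recall of a few patients for one measurement after treatment has stopped. The calculated 164 does not change. One trade-off should be accepted openly: a paused patient may be measured before completing the course. That suits an ITT comparison at a common time; results in patients who complied strictly remain the subject of the per-protocol analysis already planned.

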### Data collection

Before the first treatment session, every participant will get an assessment of both limbs by perometer, which is an automated infrared light digital scanner equipped with a microcomputer. When the limb is placed inside, the infrared light transmitters located on two sides of the perometer will be activated, and the blockage of the transmission of infrared light from both sides caused by the limb will be recorded and calculated. As the transmitters move along the limb, a series of images will be recorded. Hence a highly accurate measurement of the limb size and volume will be created. And these results will serve as the baseline data. Following the treatment of each session, participants in both groups will be asked to take assessments to get the interim data. Upon the last session, the assessments of both limbs will be adopted as the end-point data. For each arm, the measurement will repeat 3 times to ensure the reliability. Table 1 illustrates all the time points when measurements are taken during the whole procedure.

### Primary outcome

#### Absolute reduced limb volume ratio (ARLVR)

The ARLVR is the proportion of absolute reduced limb volume in the affected arm after the therapy, compared with the absolute excess volume in the affected arm before the therapy. This index is inspired by the methods established by Anderson et al. [39] With all data collected at the end of the trial, the ARLVR will be calculated using the following formula:

$$ \mathrm{ARLVR}\ \left(\%\right)=\frac{\left({\mathrm{V}}_{\mathrm{AB}}\hbox{-} {\mathrm{V}}_{\mathrm{AL}}\right)\hbox{-} \left({\mathrm{V}}_{\mathrm{UB}}\hbox{-} {\mathrm{V}}_{\mathrm{UL}}\right)}{\left({\mathrm{V}}_{\mathrm{AB}}\hbox{-} {\mathrm{V}}_{\mathrm{AL}}\right)}\times 100\% $$

In particular, V_AB_ represents the volume of affected arm with lymphedema at baseline; V_AL_ represents the volume of affected arm with lymphedema at the last session; V_UB_ represents the volume of unaffected arm at baseline; V_UL_ represents the volume of unaffected arm at the last session.

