### Sample size calculation

As no two-arm, randomized, multi-centered, sham-controlled trial has been performed on this topic, no existing data regarding the sample size are available. However, based on our preliminary clinical data collected and a similar study [41], we assume that the mean and SD of ARLVR in the real-acupuncture group and sham-acupuncture group are (0.32, 0.25) and (0.22, 0.2), respectively, and after calculation using G-Power (V.3.1), the effect size (ES) is 0.4417261. Next we input the parameters above, set the alpha risk (α, type 1 error risk) and beta risk (β, type II error risk) at 0.05 and 0.2 respectively, and choose “t test from two independent groups” and “A Priori: Compute required sample size given α, power and effect size”, then after calculating, the required sample size is 164 (Additional file 2). Assuming the loss to follow-up rate is 20%, then 197 is the total minimum sample size required in this trial. However, to increase the power and make full preparation, we decided to recruit 200 participants, 100 for each arm in this trial.

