## Discussion

BCRL can impose great burden on the society and cause significant physical and psychological morbidity to patients [42]. Despite the wide application of less invasive surgical techniques, risk for the development of BCRL still remains [43]. Current treatments options for BCRL are either expensive or rather time consuming [44]. Traditional acupuncture emerges as an efficacious, economical, and convenient choice to manage this chronic condition with few side effects, according to several pilot reports [30–35] and our clinical observation. However, after a thorough search in Pubmed and Embase for relevant articles, we found existing studies on this issue were case reports, small single-arm studies [30–33], or parallel studies using regular routine management or Diosmin as a comparison [34, 35], which cannot rule out the placebo effect and needs to be confirmed by rigorously-designed, large-scale studies. The efficacy of real acupuncture over sham acupuncture in dealing BCRL has not been fully illustrated. Therefore, additional research is required to confirm the efficacy and cost-effectiveness of acupuncture on BCRL.In this study, we will adopt Streitberger needle as the sham-acupuncture instrument. Compared with other methods such as placebo points acupuncture, shallow acupuncture at real acupoints and shallow acupuncture at placebo points, Streitberger needle have significant advantages, which make it a perfect choice to keep consistency and credibility, and avoid possible efficacy brought by placebo point acupuncture or shallow acupuncture. This method has been used in several studies with good performance, and was recommended as a reliable sham control [45–47]. Another merit of this study is the measurement instrument we choose. As pointed out above, perometer can easily and swiftly measure the volume of a participants’ limb with high reliability and minimal inter-operator variability compared with other conventional methods, such as volumeters (using a water displacement tank to measure volume) and tape measures (using a tape to measure limb circumference) [48–50], although the measurements from different methods are not interchangeable [51]. According to the data collected from patients and previous reports, the day to day variability in limb volumes is around 0.5 [52]. What is more, to better embody the real effect of acupuncture on BCRL, we use the ARLVR, a more reasonable and practical index that is calculated based on the surplus between the affected arm and the contralateral arm. Theoretically, it can exclude the interfering factors such as base effect and weight fluctuation.

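### The printed ARLVR formula divides by the affected arm's own change, not by its baseline excess, so a patient with a stable unaffected arm scores 100% whatever happens to the lymphedema

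*Protocol article*

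**What the plan says.** The protocol article, under Primary outcome (ARLVR), describes the index as the reduction in affected-arm volume "compared with the absolute excess volume in the affected arm before the therapy". It then says the value will be computed from the formula that follows:

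ARLVR = [(V_AB − V_AL) − (V_UB − V_UL)] / (V_AB − V_AL) × 100%

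The legend states that V_AL "represents the volume of affected arm with lymphedema at the last session" and that V_UB "represents the volume of unaffected arm at baseline". V_AB and V_UL are the affected arm at baseline and the unaffected arm at the last session.

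Two other places bear on the meaning:

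- The Discussion presents ARLVR as an index "calculated based on the surplus between the affected arm and the contralateral arm".
- The sample size section assumes that "the mean and SD of ARLVR in the real-acupuncture group and sham-acupuncture group are (0.32, 0.25) and (0.22, 0.2), respectively", and reports that "the effect size (ES) is 0.4417261".

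**The concern.** A quantity fixed before therapy cannot contain a last-session measurement, yet the printed denominator contains V_AL. It repeats the first bracket of the numerator and includes no volume from the contralateral arm. The words and the formula therefore define two different primary endpoints.

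If the formula is applied as printed, the endpoint no longer measures how much of the excess volume was removed. It becomes a ratio whose denominator can be close to zero or negative, and the power calculation does not apply to it. If the error is noticed only after unblinding, correcting it will look like a change of primary endpoint.

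**Working it through.** **1. The plan's own figure.** From the sample size section: means 0.32 and 0.22, SDs 0.25 and 0.20, and alpha and beta ("type II error risk) at 0.05 and 0.2 respectively").

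- Effect size = (0.32 − 0.22) / √[(0.25² + 0.20²)/2] = 0.10 / √0.05125 = 0.4417, as stated.
- A two-sided t test (noncentral t) needs 82 per arm, 164 in total, with power 0.803. The stated 164 is reproduced.

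**2. Algebra on the printed formula.**

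[(V_AB − V_AL) − (V_UB − V_UL)] / (V_AB − V_AL) = 1 − (V_UB − V_UL)/(V_AB − V_AL)

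If V_UB = V_UL, this is 1 for any non-zero change in the affected arm. If V_AB = V_AL, it is undefined.

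**3. Worked example.** Assume an unaffected arm stable at 2000 mL and V_AB = 2500 mL, so the baseline excess is 500 mL (25%, within the 10–40% entry range).

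| V_AL (mL) | Printed formula | Denominator V_AB − V_UB |
|---|---|---|
| 2340 | 160/160 = 100% | 160/500 = 32% |
| 2390 | 110/110 = 100% | 110/500 = 22% |
| 2500 | 0/0, undefined | 0/500 = 0% |
| 2600 (worse) | −100/−100 = 100% | −100/500 = −20% |

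Now hold the net reductions at 160 and 110 mL and let the unaffected arm move:

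- It loses 10 mL: the printed values are 160/170 = 94.1% and 110/120 = 91.7%.
- It gains 10 mL: they are 160/150 = 106.7% and 110/100 = 110.0%, so the better result gets the lower score.

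**4. Do the planning means fit the printed formula?** To give 0.32 and 0.22, the ratio (V_UB − V_UL)/(V_AB − V_AL) would have to be 1 − 0.32 = 0.68 and 1 − 0.22 = 0.78. The healthy arm would have to lose about 68% and 78% of what the swollen arm loses.

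**5. Simulation.** 82 per arm, 1500 runs per scenario, net reduction drawn from the plan's means and SDs. Assumptions not in the article: unaffected arm 2000 mL, excess uniform over 10–40%, and the unaffected-arm changes shown. Entries in the last three columns are rejection rates at 0.05.

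| Unaffected-arm change, mean (SD), mL | Printed: medians real / sham | Printed: t test | Printed: rank test | Verbal: t test |
|---|---|---|---|---|
| 0 (2 to 40) | 0.97–1.00 / 0.94–1.00 | 0.02 | 0.05–0.08 | 0.79–0.82 |
| gain 10 (10) | 1.05 / 1.06 | 0.015 | 0.06 | 0.80 |
| gain 20 (20) | 1.09 / 1.10 | 0.03 | 0.06 | 0.83 |
| loss 10 (10) | 0.95 / 0.93 | 0.02 | 0.12 | 0.79 |
| loss 20 (20) | 0.90 / 0.87 | 0.035 | 0.19 | 0.80 |
| loss 40 (10) | 0.80 / 0.74 | 0.05 | 0.51 | 0.81 |

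At the recruited 100 per arm, with a stable unaffected arm, the verbal denominator gives power of 86–87% (t test) and 84–85% (rank test). The printed one rejects in about 2% and 5% of runs, with a median of 1.00 in both arms.

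**The case against.** The strongest reply is that this is a slip in one symbol, V_AL for V_UB. The wording, the Discussion and the planning means all point to the intended index, and no analysis program is shown, so the trial may well compute the right quantity. That is plausible. But the article says ARLVR will be calculated with this formula, and nothing elsewhere corrects it.

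Other points limit how strongly the consequence can be put:

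- A value near 100% in both groups requires an unaffected arm that changes little. The article gives no figure for this, and both arms are needled. This stands as a condition.
- The analysis section allows a nonparametric test, and an unstable ratio would probably lead to it. A rank test regains some power if the unaffected arm shrinks systematically, up to 0.51 in the most extreme scenario. That signal still does not measure reduction of the excess.
- Division by zero under last observation carried forward should be uncommon. Volumes are taken after every session and an evaluation is attempted at withdrawal, so few patients should have only a baseline.
- The verbal definition mentions only the affected arm's reduction, while the printed numerator also subtracts the unaffected arm's change. The Discussion supports the net version, but the sponsor should confirm it.

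**Conclusion.** The concern holds. The primary endpoint is defined one way in words and another way in the formula, and the formula is the wrong one. This follows from the outcome section alone, and the reduction to 1 − (V_UB − V_UL)/(V_AB − V_AL) needs no assumption.

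The size of the damage does rest on assumptions about arm volume and unaffected-arm change. Across the range tried, the planned t test has essentially no power on the printed ratio, and the rank test has little unless the unaffected arm shrinks markedly. The stated power belongs to the verbal definition only. Because the error is in the primary endpoint, it must be corrected before analysis.

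**What to change.** Replace the denominator so that the formula reads:

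ARLVR (%) = [(V_AB − V_AL) − (V_UB − V_UL)] / (V_AB − V_UB) × 100%

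The numerator then equals (V_AB − V_UB) − (V_AL − V_UL), baseline excess minus final excess. State in the text that the reduction is net of the change in the unaffected arm. The entry criterion of at least 10% excess keeps the denominator positive, and a patient with only a baseline carried forward scores 0% instead of an undefined value.

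Make the correction in the protocol, and in the analysis plan, program and any other record that repeats the formula, before unblinded data are analysed. It needs no extra patients or measurements. The required 164 before allowance for loss is unchanged, because the planning values already suit this definition.
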